## **16. Study Monitoring**

The study will be monitored by an internal Safety Review Committee (SRC), an Independent Data and Safety Monitoring Committee (IDSMC) and an Independent Medical Monitor. Because of the infection prevention and control implemented at COVID-19 treatment centres, a virtual monitoring plan will be implemented.

### **16.1. Safety Review Committee (SRC)**

The SRC will monitor the conduct of the study through weekly summary reports of enrolment, baseline characteristics, laboratory results, adverse events, protocol deviations, reasons for premature discontinuations and adverse events. On a weekly basis, one of the investigators designated as the internal safety monitor who is also member of the SRC will review by-arm summaries of premature study discontinuations and premature study treatment discontinuations (and reasons) and AEs. A detailed description of the operational aspects of the SRC, including membership, will be documented in the SRC Charter.

### **16.2. Independent Medical Monitor**

The independent monitor will conduct up to four visits: one pre-study, two routine and close out monitoring visits. The first routine monitoring visit will occur as soon as the first participant is recruited or within 2 weeks of the first participant is recruited. During each visit, the monitor will review the individual participant records for prospectively identified critical data and processes that if inaccurate, not performed, or performed incorrectly, would threaten the protection of human subjects or the integrity of the study results. These include verification that informed consent was obtained appropriately, adherence to protocol eligibility criteria, documentation of study drug accountability and administration, conduct and documentation of procedures and assessments related to study endpoints, protocol-required safety assessments, adverse events documentation and reporting, as well as other procedures essential to trial integrity. The independent monitor also will inspect regulatory files for all study sites to ensure compliance with regulatory requirements, and the sites' pharmacies to review product storage and management. These activities are described in the Monitoring Plan and SOP.

### **16.3. Independent Data and Safety Monitoring Committee (IDSMC)**

The IDSMC will include individuals with expertise in respiratory viruses, antiviral therapies and shedding, emerging epidemics, and biostatistics. The IDSMC will monitor the trial for safety, operational futility, and efficacy. The IDSMC will also conduct periodic assessments of factors that can affect project implementation, including accrual, retention, performance and variation across sites. IDSMC meetings will be by teleconference. Open reports containing accrual and retention rates, participant characteristics, and serious adverse events (SAEs) will be sent to the protocol team and IDSMC members a week ahead. All safety issues will be reviewed by the IDSMC after the first 30 participants have completed 14 days of follow up and when any grade 3 or higher adverse event occurred in the intervention group. A detailed description of the operational aspects, including membership, will be documented in the IDSMC Charter.

## **17. Treatment Discontinuation and Withdrawal From Trial**

### **17.1. Discontinuation**

Study treatment may be discontinued for any of the following reasons:

- Request to terminate study treatment by participant

- Need to start concomitant medications known to interact with study intervention
- Development of any contraindication to study drug
- An adverse event that necessitates discontinuation of study drug
- Other reasons believed by the clinical investigators or primary care providers to place the participant at risk.

Where participants stop study intervention, they may continue in the trial off study drug with continued evaluations. The reason for study drug discontinuation will be documented.

## **17.2. Withdrawal from the trial**

Although a participant is not obliged to explain their reason for withdrawing prematurely from a trial, reasonable effort will be made to ascertain the reason while fully respecting the participant's rights. Additionally, the investigators may withdraw a participant from the trial for any of the following reasons:

- Decision of the ethics committees or the regulatory agency as part of their duties, clinical investigators or primary care providers if they think continued participation is no longer in the best interest of the participant.
- If failure to comply with the protocol requirements by the participant puts them or the reliability of resulting data at risk.
- If a participant leaves the isolation and treatment centre (study site) against medical advice, they will be considered lost to follow-up and the following actions will be taken:
  - The site clinical investigator (or a designated member of the study team) will attempt to contact the participant as soon as possible and counsel the participant on the need to follow the national COVID-19 case management guidance.
  - The caller will ascertain whether or not the participant wishes to continue in the trial and return to the isolation and treatment centre to facilitate this. Arrangement to return participants to site will be as per existing SOP of the NCDC.
  - Where possible, up to 2 telephone call attempts per day must be made to the participants usual mobile number or their next of kin (if necessary) in the 3 days following a participant's absence from site before a participant will be deemed lost to follow-up. A participant who is unreachable after these efforts will be withdrawn from the study due to lost to follow-up.

Any data collected before such withdrawal of consent will be retained and used. Withdrawing participants will have the right to request destruction of any samples taken and not yet tested. Such requests will be documented by the site investigator. Whenever possible, follow up assessments scheduled for day 28 study exit visit will be completed at the time of withdrawal or discontinuation.

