### **3.4. Follow-up**

The treatment duration for participants in the intervention group will be 14 days. However, follow up will continue until day 28 after study entry at the end of which all participants will exit the study. The schedule of activities during the follow up period is presented in Table 1. Participants who stop study product should continue study participation off study product with continued evaluations as per the schedule of activities. The reason for study product discontinuation should be recorded. Daily survey, vital signs and SpO2 as well as Flu-PRO questionnaire will be recorded by participant (both on paper and cloud-based forms using their mobile device while connected to the internet). SpO2 will be measured after at least 5 minutes resting in a sitting or supine position. Participants with an SpO2 below 93% will repeat the assessment 2 hours later. If the repeat assessment is still below 93%, study clinician will be alerted.

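### Section 17.2 lets investigators end a participant's follow-up because non-compliance threatens data reliability, which conflicts with the continue-off-drug rule in Section 3.4 and invites avoidable, possibly informative loss of outcome data

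*Protocol*

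**What the plan says.** Three places in the protocol govern what happens when a participant departs from the plan.

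- **Section 3.4 (Follow-up):** "Participants who stop study product should continue study participation off study product with continued evaluations as per the schedule of activities".
- **Section 17.1 (Discontinuation):** after stopping the intervention, "they may continue in the trial off study drug with continued evaluations". One of its grounds for stopping drug is: "Other reasons believed by the clinical investigators or primary care providers to place the participant at risk".
- **Section 17.2 (Withdrawal from the trial):** "the investigators may withdraw a participant from the trial for any of the following reasons". Two of those reasons matter here. The first is non-compliance: "If failure to comply with the protocol requirements by the participant puts them or the reliability of resulting data at risk". The second is a judgement by "clinical investigators or primary care providers if they think continued participation is no longer in the best interest of the participant".

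Section 17.2 closes with two provisions on data. The first is: "Any data collected before such withdrawal of consent will be retained and used". The second is: "Whenever possible, follow up assessments scheduled for day 28 study exit visit will be completed at the time of withdrawal or discontinuation".

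**The concern.** Stopping study drug and ending participation are different events, and Section 17 has separate subsections for them. The rules nevertheless overlap. A patient who skips or refuses tablets has in effect stopped product (Section 3.4: keep evaluating). The same patient has also failed a protocol requirement (Section 17.2: may be withdrawn if data reliability is thought to be at risk). A clinician's concern for the patient appears under 17.1, where it stops drug only, and in similar terms under 17.2, where it ends participation. The four sites could handle the same patient differently.

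Data reliability is a poor reason to stop collecting outcomes. Non-adherence after randomisation is part of what the randomised comparison should capture, and ending follow-up because of it makes missingness depend on tolerability and clinical course. Staff know the allocation, and only the intervention arm has a drug regimen that can be failed. The outcomes exposed are PCR status and viral load at the later sampling days, time to clinical improvement, and Day 28 mortality. An analysis plan cannot recover results that were never obtained.

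**Working it through.** The point rests mainly on the text, so the provisions come first and the arithmetic after.

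**1. The provisions side by side**

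| Situation | 3.4 | 17.1 | 17.2 |
|---|---|---|---|
| Participant stops study drug | Evaluations *should* continue | Participant *may* continue | Day 28 assessments brought forward at discontinuation, where possible |
| Non-compliance thought to threaten the data | Not addressed | Not addressed | Investigator may withdraw from the trial |
| Clinician judges the participant to be at risk, or not best served | Not addressed | Drug may be stopped | Participation may be ended |

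The first row holds three different instructions for one event. The word discontinuation in 17.2 could mean discontinuing participation. Section 17, however, uses it as the title of 17.1, where it means stopping treatment.

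**2. What an early exit loses**

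Table 1, footnote 2, schedules viral samples on Days 0, 2, 4, 6, 7, 14 and 28. Take a participant withdrawn on Day 5. The Day 0, 2 and 4 samples are kept and an exit assessment may be made on Day 5. The Day 6, 7, 14 and 28 samples are not taken. An assessment on Day 5 cannot stand in for Day 28 PCR status, Day 28 mortality or a later clinical improvement.

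**3. Exposure by arm**

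Sections 3.2.1 and 3.4 give nitazoxanide twice daily and atazanavir/ritonavir once daily for 14 days: 2 × 14 = 28 and 1 × 14 = 14 administrations in the intervention arm, and none in the control arm. Vital signs, questionnaires, sampling and remaining on site apply to both arms.

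**4. The one stated figure that touches loss**

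Section 6 plans 89 patients plus 10%: 89 × 1.10 = 97.9, rounded to 98, as stated. The allowance is 98 − 89 = 9 patients, for all causes and both arms. Five withdrawals under this clause would use more than half of it.

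**5. Illustration of size (assumed inputs)**

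The protocol gives no adherence or response rates. Both scenarios below assume 49 per arm (Synopsis), withdrawals in the intervention arm only, and withdrawn patients left out of the analysis altogether.

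*Scenario A.* Compliers are 70% PCR negative; *n* patients with true rate *r* are withdrawn. Full-arm rate = ((49 − *n*) × 0.70 + *n* × *r*)/49.

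- *n* = 5, *r* = 0.3: (30.8 + 1.5)/49 = 65.9%, so the arm reads 4.1 points too high.
- *n* = 5, *r* = 0.5: (30.8 + 2.5)/49 = 68.0%, so 2.0 points too high.
- *n* = 10, *r* = 0.3 to 0.5: 61.8% to 65.9%, so 8.2 to 4.1 points too high.

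*Scenario B.* No true effect, 50% negative in each arm, and a fraction *q* withdrawn of whom a proportion *r* would be negative. Observed intervention rate = (0.50 − *q* × *r*)/(1 − *q*). The type I error is a normal approximation at two-sided 5%.

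| *q* | *r* | Spurious difference (points) | Type I error |
|---|---|---|---|
| 5% | 0.4 to 0.2 | 0.5 to 1.6 | 5.0% to 5.3% |
| 10% | 0.4 to 0.2 | 1.1 to 3.3 | 5.1% to 6.2% |
| 20% | 0.4 to 0.2 | 2.5 to 7.5 | 5.6% to 10.8% |

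Worked case, *q* = 10%, *r* = 0.2: (0.50 − 0.02)/0.90 = 53.3%, a difference of 3.3 points.

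The sign depends on *r*. If the withdrawn patients do better (*r* = 0.6, *q* = 10%), the rate is (0.50 − 0.06)/0.90 = 48.9%, a difference of −1.1 points, against the intervention.

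**The case against.** A reader might infer that Section 17.2 flatly contradicts Section 3.4, selectively removes non-adherent patients from the intervention arm, and so biases efficacy and safety in favour of the drug. The documents do not support that much.

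- **Different triggers.** Section 3.4 concerns stopping product. Section 17.2 concerns failing protocol requirements, is discretionary, and applies only where the participant or the data are put at risk. A patient who refuses tablets because of nausea fits the grounds in 17.1 more naturally. The conflict is one of overlapping rules with no stated order of precedence.
- **Both arms are bound.** The clause is not limited to study drug. Imbalance between arms is a reasonable inference, since only one arm takes drug, but the protocol does not state it.
- **Withdrawn patients are not erased.** Earlier data are retained, at least after withdrawal of consent; the sentence does not clearly cover withdrawal by the investigator, but nothing provides for discarding those data either. An exit assessment is attempted. Section 21 requires adverse events to be followed until they subside, and possibly related ones even after participation ends, so a general loss of safety data cannot be claimed. A withdrawn patient still contributes time before withdrawal to the time-to-event analysis.
- **The size is modest and assumed.** Using 70% in both arms, the standard error of a difference is √(2 × 0.7 × 0.3/49) = 9.3 points, against a shift of 2 to 4 points with five patients withdrawn. Complete exclusion is prescribed nowhere, and the analysis population may be set in the statistical analysis plan.

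These points limit the size and certainty of the effect. They do not remove the inconsistency between the sections, and they do not supply the outcomes missed after an early exit.

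**Conclusion.** The concern stands in a limited form. Sections 3.4, 17.1 and 17.2 give overlapping and conflicting instructions for a participant who stops drug or complies poorly. The data-reliability ground permits outcome follow-up to be ended when it need not be. The resulting loss could be informative and, because only one arm has a drug regimen in an open-label trial, could differ between arms.

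Neither size nor direction can be derived from the protocol. With 10% of one arm withdrawn and left out of the analysis, the two illustrations give about 1 to 4 percentage points, with type I error of 5.1% to 6.2% in the no-effect scenario. These figures rest on assumed response rates, one-sided withdrawal and complete exclusion; retaining earlier data would reduce them. They favour the intervention only if non-adherent patients do worse, and reverse if they do better.

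The case for acting is that the lost data cannot be recovered at the analysis stage and the correction is cheap.

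**What to change.** Reconcile the three sections:

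1. In 17.2, remove data reliability (non-compliance alone) as a ground for ending outcome follow-up. State that non-compliance, or stopping study drug, leads to continued scheduled evaluations to Day 28, subject to the participant's consent.
2. In 17.1, replace the permission to continue with the expectation already stated in 3.4.
3. In the last sentence of 17.2, limit the brought-forward Day 28 assessments to true withdrawal from the trial.
4. Leave the participant-safety and best-interest grounds to the investigators. Ask only that the overlap between 17.1 and 17.2 be reconciled, so that it is clear which judgement stops drug and which ends participation.

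The cost is a wording amendment. A few more patients would complete assessments already in the schedule.

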## 9. Specimen Collection for SARS-CoV-2 Viral Load

Saliva will be self-collected by participants under supervision into 15 mL screw-cap tubes from which 1.5-2mL will be transferred into 2 mL cryo vials for SARS-CoV-2 viral load determination. Where necessary nasopharyngeal swab specimen will be collected using Dacron® or Copan® polyester flocked swabs. Insert flexible wire shaft minitip swab through the nares parallel to the palate (not upwards) until resistance is encountered or the distance is equivalent to that from the ear to the nostril of the patient, indicating contact with the nasopharynx. Swab will reach a depth equal to distance from nostrils to outer opening of the ear and gently rubbed and rolled. Swab will be left in place for at least 15 seconds to absorb secretions and then slowly removed while being rotated.

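### Section 17.2 gives two conflicting rules for a participant who leaves against medical advice, and no follow-up route for one who is reachable and consents but will not return

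*Protocol*

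**What the plan says.** The opening of the bullet in Protocol Section 17.2 states that if a participant "leaves the isolation and treatment centre (study site) against medical advice, they will be considered lost to follow-up". Its sub-items then describe tracing. The site tries to make contact, and the caller finds out whether the participant "wishes to continue in the trial and return to the isolation and treatment centre to facilitate this". Up to two calls a day are to be made, where possible, "in the 3 days following a participant's absence from site before a participant will be deemed lost to follow-up". The bullet ends: "A participant who is unreachable after these efforts will be withdrawn from the study due to lost to follow-up".

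For anyone withdrawn or discontinued, Section 17.2 adds: "Whenever possible, follow up assessments scheduled for day 28 study exit visit will be completed at the time of withdrawal or discontinuation".

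Section 3.4 runs follow-up to Day 28 and says that participants who stop study product should remain in the study with their scheduled evaluations (Section 17.1 says they may). It also says that the daily survey, vital signs, SpO2 and Flu-PRO "will be recorded by participant (both on paper and cloud-based forms using their mobile device while connected to the internet". Table 1 schedules daily vitals, Flu-PRO and adverse event monitoring at Days 21 and 28 as well as during treatment. Section 9 says of the virology specimen: "Saliva will be self-collected by participants under supervision".

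Section 12 states censoring at Day 28 and gives no rule for earlier loss. Section 5 makes hospital discharge one of the two events that count as clinical improvement.

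**The concern.** Two things are wrong on the page. First, Section 17.2 defines loss to follow-up twice for the same person: by departure, and by failed contact. Sites could record the same event with different statuses and dates. Second, the call puts one joined question, continue and return. A participant who would accept the first but not the second is not provided for.

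The protocol treats stopping treatment and leaving the building differently, although neither is a withdrawal of consent. The first keeps the participant in follow-up. The second ends it unless the participant goes back.

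At stake are Day 28 mortality, time to death, time to symptom resolution by Flu-PRO, and adverse events up to Day 28. Allocation is known to everyone, so a decision to leave could depend on symptoms and on the arm. Missing data that arise this way may be informative. It is also left open whether leaving against advice counts as discharge, and so as an improvement event, in time to clinical improvement. An analysis plan could settle the coding of discharge. It could not recover outcomes that the protocol tells sites to stop collecting.

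**Working it through.** **1. The two rules applied to the possible cases**

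| Case | Opening sentence of the bullet | Sub-items of the same bullet |
|---|---|---|
| Leaves, unreachable after the calls | Lost on leaving | Lost after up to 3 days of calls |
| Leaves, reachable, returns | Lost on leaving | Continues in the trial |
| Leaves, reachable, consents to follow-up, will not return | Lost on leaving | Not unreachable, so not lost, but no way to continue is offered |

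In the first case the rules agree on status and differ on date by up to 3 days. In the second they contradict each other. In the third neither rule leads to follow-up. For comparison, a participant who stops study product stays in scheduled follow-up under Section 3.4.

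**2. What could still be collected in the third case**

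- Flu-PRO: already self-recorded on paper and mobile forms (Section 3.4).
- Vital signs and SpO2: also self-recorded, but only if the participant has the means to measure them away from the centre, which the protocol does not describe.
- Adverse events and Day 28 vital status: can be obtained by phone. Section 17.2 already has staff calling the participant or next of kin.
- PCR and viral load: not covered, because saliva collection is supervised (Section 9).
- Safety blood samples: not covered.
- Ordinal scale: off-site scoring by a clinician is not described.

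Bringing the Day 28 assessments forward to the time of withdrawal cannot supply vital status at Day 28.

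**3. The one stated figure on loss**

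Section 6 allows 10% loss on 89 participants and arrives at 98.

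- 89 × 1.10 = 97.9, rounded up to 98, which reproduces the plan's figure.
- 89 / 0.90 = 98.9, rounded up to 99, within one participant.
- 10% of 98 is 9.8, leaving 88.2.

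This allowance covers loss from every cause. The protocol does not say how much of it would be departure against advice, or how it would split by arm.

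**4. Can a direction of bias be derived?**

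Assume no treatment effect, with 80% improved by Day 28 in both arms. Let L be the fraction lost in an arm and r the improvement rate among those lost. The rate observed in those retained is (0.80 − L·r)/(1 − L). All inputs here are assumptions.

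- L = 20% control and 5% intervention, r = 95%: control (0.80 − 0.19)/0.80 = 76.3%; intervention (0.80 − 0.0475)/0.95 = 79.2%; difference +3.0 points (from unrounded rates).
- Same losses, r = 50%: control (0.80 − 0.10)/0.80 = 87.5%; intervention (0.80 − 0.025)/0.95 = 81.6%; difference −5.9 points.
- L = 10% in both arms, r = 50%: (0.80 − 0.05)/0.90 = 83.3% in both; difference 0.

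The sign depends on who leaves, and in this setting equal loss with equal prognosis gives no bias. The protocol fixes none of these inputs.

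**The case against.** The strongest defence is that the opening sentence is only a provisional label that triggers tracing. The sub-items seek contact, arrange return and withdraw only the unreachable, and the surrounding list is permissive because investigators may withdraw. This is fair. A reader might infer that everyone who leaves is dropped even if reachable and willing. The protocol does not support that, because a participant who returns can continue. What survives is the wording conflict and the participant who is reachable but will not return.

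A second objection is that the existing tools do not amount to home follow-up. Section 8 presents self-monitoring as a way to limit exposure, and Section 4 has the attending physician and centre staff eliciting adverse events. A reader might infer that the remote forms could rescue every outcome. They could not: two of the three primary outcomes are virological and need supervised samples. The objection stands for those outcomes, for blood samples and for ordinal scoring. It does not stand for Flu-PRO, phone-reported adverse events or vital status.

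Third, the loss of safety data is not total. Section 21 requires adverse events judged possibly related to study medication to be followed after participation ends, and later related events to be reported. That stands, but it does not secure unrelated events or Day 28 vital status.

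Fourth, the protocol gives no reasons for leaving and no censoring rule for early loss, and the latter may sit in an analysis plan. A reader might therefore go too far in concluding that outcomes are censored because of how patients feel, or that the false-positive rate is inflated by a known amount. Such a figure would need an assumed arm split, an assumed prognosis of leavers and an assumed link between leaving time and recovery. The protocol supplies none of them.

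**Conclusion.** The point holds in a limited form. Section 17.2 contradicts itself on when a participant who leaves against advice is lost, and it provides no follow-up for one who is reachable and consents but will not return. If the section is followed as written, Day 28 vital status, Flu-PRO and adverse event data that could be had by phone or on existing forms are given up. That the loss could be informative is a reasonable inference from the open-label design, not something the protocol shows. Neither its size nor its direction can be derived: the illustrative shifts of +3.0 and −5.9 points come entirely from assumed inputs, and no hazard ratio or type I error figure is warranted. The case for change rests on the conflict and on how cheaply the data could be kept.

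**What to change.** Reconcile the bullet in Section 17.2 so that leaving the site is not in itself loss to follow-up. Suggested content:

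- A participant who leaves against medical advice and does not withdraw consent stays in the trial.
- Flu-PRO and adverse events continue on the existing self-report forms or by phone. Vital signs and SpO2 are recorded where the participant can measure them.
- Vital status is obtained by phone at Day 28 from the participant or next of kin.
- Only a participant who is unreachable after the stated calls is lost to follow-up.
- Leaving against advice does not count as discharge in time to clinical improvement (cross-refer in Section 5).

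Whether the participant should return to the centre stays with existing guidance and is not part of this change.

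The cost is protocol wording and a few extra calls. The limit is that saliva or swab samples for PCR and viral load, blood samples and clinician ordinal scores may still be missing for these participants.

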Abbreviations: ECMO, Extracorporeal membrane oxygenation; NIV, Non-invasive ventilation;  $\text{FiO}_2$ , Fraction of inspired oxygen;  $\text{PaO}_2$ , pressure of arterial oxygen;  $\text{SpO}_2$ , oxygen saturation

- Time to PCR negativity. Proportion of participants with SARS-CoV-2 polymerase chain reaction (PCR) negative result at Days 7, 10, 14 and 28.
- Temporal patterns of SARS-CoV-2 viral load quantified by RT-PCR from nasal swabs or sputum of patients receiving SOC alone versus SOC plus study drug.

Secondary outcome measures:

- Time to symptoms resolution as monitored by the inFLUenza Patient-Reported Outcome (FLU-PRO) questionnaire with some modifications for COVID-19 (Appendix 8).
- Clinical status as assessed with the 10-category ordinal scale on days 7 and 14
- Duration of hospitalization in survivors
- Day 28 mortality
- Time from treatment initiation to death
- Proportion with viral RNA detection over time

 Note:  $\text{PaO}_2/\text{FiO}_2$  of 200-300, mild ARD; 100-200, moderate ARD; <100, severe ARD

Safety outcome measures:

- Adverse events during treatment
- Serious adverse events (respiratory failure or Acute Respiratory Distress Syndrome (ARDS), acute kidney Injury (AKI), secondary infection, shock, severe anemia, acute gastritis, unconsciousness, sepsis, acute heart failure)
- Gastrointestinal adverse events (nausea, vomiting, and diarrhea)
- Premature discontinuation of treatment

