## 6. Power and Sample Size Determination

As shown in Figure 3, the sample size estimation is based on the assumption that an improvement of at least 60-80% in time to SARS-CoV-2 PCR negativity and symptoms resolution can be achieved in the intervention group compared with the control group. Hence, a total sample size of 89 will provide at least 80% power to show or exclude 60% improvement in time to SARS-CoV-2 PCR negativity. This assumes a two-sided and 5% type 1 error rate. Therefore, providing for a 10% loss to follow up rate, a total of 98 patients will be recruited.

[figure not shown]

**Figure 3.** Power calculation and sample size estimation.

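### Section 17.2 ends all follow-up of participants who leave against medical advice and stay unreachable for 3 days, so their Day 28 vital status is never sought

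*Protocol*

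**What the plan says.** Protocol section 17.2 lists grounds on which investigators may withdraw a participant. The third concerns departure from the site: "If a participant leaves the isolation and treatment centre (study site) against medical advice, they will be considered lost to follow-up". Calls are then made to the participant's usual number, or to next of kin if necessary, at most twice a day and where possible, "in the 3 days following a participant's absence from site before a participant will be deemed lost to follow-up". The closing rule is mandatory: "A participant who is unreachable after these efforts will be withdrawn from the study due to lost to follow-up".

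The section offers one mitigation: "Whenever possible, follow up assessments scheduled for day 28 study exit visit will be completed at the time of withdrawal or discontinuation".

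Elsewhere, section 3.4 states that "follow up will continue until day 28 after study entry at the end of which all participants will exit the study". Section 5 lists "Day 28 mortality" and "Time from treatment initiation to death" among the secondary outcomes. Section 6 sets the sample size "providing for a 10% loss to follow up rate". Sections 3.4 and 17.1 provide for participants who merely stop study drug to remain under evaluation.

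**The concern.** Failing to answer the telephone for 3 days is not withdrawal of consent. Someone who has left the centre and cannot be reached may be well, readmitted elsewhere or dead, so their missing outcome is unlikely to be a random omission. In an open-label trial, the reasons for leaving may also differ between arms.

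Once such a participant is withdrawn, no section of the protocol provides for a call at Day 21 or Day 28, a later approach to next of kin, or a check of records. An analysis plan can choose how to handle unknown vital status, but it cannot recover information that sites were told to stop seeking. The Day 28 mortality comparison and the time-to-death analysis are at stake.

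**Working it through.** **1. The rule against the outcomes it affects**

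| Place in the protocol | Effect on an unreachable participant |
|---|---|
| 17.2, calls | At most 2 × 3 = 6 calls; no minimum is stated; next of kin included |
| 17.2, closing rule | Withdrawn from the whole study, not only from study drug |
| 17.2, early exit assessments | Cannot be done for someone who cannot be reached; status at an early withdrawal is not Day 28 status in any case |
| 3.4 | Follow-up is meant to run to Day 28 |
| 5 | Day 28 mortality and time to death are to be reported |

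As an illustration with an assumed date, a participant who leaves on Day 10 and is not reached would be withdrawn at about Day 13. That is 28 − 13 = 15 days before the outcome date, with no planned contact in between.

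The wording of 17.2 is also unsettled. A participant who leaves is classed as lost at once in one sentence and only after 3 days of calls in another. The paragraph that follows describes these cases as withdrawal of consent, which an unreachable participant has not given.

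**2. The plan's own loss figure**

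Inputs from section 6: 89 evaluable, 10% loss, 98 recruited. From the synopsis: 49 per arm.

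- Reproduction: 89 × 1.10 = 97.9, rounded up to 98, which matches the plan. Dividing instead gives 89 / 0.90 = 98.9, or 99. The difference of one participant does not matter here.
- Implied losses: 98 − 89 = 9.

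**3. Upper illustration for overall Day 28 mortality**

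Suppose all 9 losses have unknown vital status. With d deaths among the 89 with known status, the best case over all 98 is d/98 and the worst case is (d + 9)/98. The width is 9/98 = 9.2 percentage points whatever d is. The protocol gives no mortality rate, so d is assumed over a range.

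| Deaths among 89 (assumed) | Observed | Best case | Worst case |
|---|---|---|---|
| 2 | 2.2% | 2/98 = 2.0% | 11/98 = 11.2% |
| 4 | 4.5% | 4/98 = 4.1% | 13/98 = 13.3% |
| 9 | 10.1% | 9/98 = 9.2% | 18/98 = 18.4% |
| 13 | 14.6% | 13/98 = 13.3% | 22/98 = 22.4% |

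**4. By arm**

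- Losses split 4 and 5: the arm rates are uncertain by 4/49 = 8.2 and 5/49 = 10.2 points.
- All 9 in one arm: 9/49 = 18.4 points for that arm and none for the other.

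These are extreme bounds, since they let every unknown be alive or every unknown be dead.

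**The case against.** The case against making much of this is substantial, and most of it limits the size of the point.

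- **Scope.** A reader might infer that any participant unreachable for 3 days is withdrawn. The text does not support that. The sentence sits under departure against medical advice and does not cover inpatients or participants properly discharged.
- **Next of kin.** The 3-day calls may already go to next of kin, so a death in that window can be learned. The gap is what happens afterwards.
- **Size.** A reader might take the 10% allowance as the number this rule will lose. It is an all-cause allowance attached to a sample size for PCR negativity. The protocol does not say what share would come from leaving and staying unreachable, so 9 of 98 is a ceiling for illustration.
- **Time to death.** Data collected before withdrawal are retained, so this outcome is censored at last contact rather than lost. The complaint is possible informative censoring, which is narrower.
- **Later events.** A reader might infer that all later deterioration goes unrecorded. Section 21 still asks for later events judged related to study drug to be reported, and for possibly related events to be followed after participation ends. That qualifies the inference, but it is not active tracing and does not provide vital status for everyone.
- **Stakes.** Both mortality outcomes are secondary in a 98-patient pilot, and patients needing mechanical ventilation at screening are excluded. Nothing in the protocol rests a decision on the direction of the mortality comparison.

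None of this supplies an attempt to establish vital status after the third day.

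**Conclusion.** The point holds for a defined group: participants who leave the centre against medical advice and are not reached, directly or through next of kin, within 3 days. For them the protocol as written ends follow-up without withdrawal of consent. Day 28 mortality is then unknown and time to death is censored at last contact, possibly informatively given open-label allocation.

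The number affected cannot be derived from the document. At most, if the whole loss allowance arose this way, overall Day 28 mortality would carry 9.2 points of best-to-worst-case uncertainty. The true contribution of this rule may be much smaller. The conclusion that no later attempt is planned rests on the protocol's silence after a mandatory withdrawal. The consent documents are not available, so whether they would already permit later contact cannot be checked.

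This is a modest defect in secondary outcomes, worth correcting because the correction is cheap. It does not bear on the sample size.

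**What to change.** In section 17.2, keep the 3-day calls. In the closing sentence on unreachable participants, keep the subject and replace the rest with:

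> will be recorded as currently unreachable; unless consent has been withdrawn or the participant is withdrawn on another ground in this section, contact with the participant or next of kin will be attempted again at Day 28 (and, where feasible, Days 14 and 21), within the consent given, at least for vital and hospital status; lost to follow-up is assigned only if the Day 28 attempt fails.

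The exception for other grounds is needed because 17.2 also allows withdrawal by ethics committees, the regulator or clinicians, and for non-compliance. A rule that only withdrawal of consent ends follow-up would contradict those provisions. The two other places in the same bullet that assign lost-to-follow-up status should be aligned with the new wording.

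The cost is a few extra calls to contacts the section already relies on, and a check that the consent covers them. Days 14, 21 and 28 are already visit days in Table 1. The sample size and treatment are unchanged.
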